## **PROJECT SUMMARY**

MELAS patients suffer from exercise intolerance, weakness, poor vision or blindness, poor growth, developmental delay, and deafness. They also have unique 'stroke-like' episodes (SLEs) which are not due to blockages of large or medium arteries. These 'strokes' are thought to be due to energy failure of very small brain blood vessels combined with energy failure in the mitochondria (cell battery) of the brain cells, especially in the back region of the brain in the vision centre. This leads to visual loss and paralysis. The overall goal of this grant is to better understand the mechanism of these SLEs at the level of the brain cells and small blood vessels. To do this, we will study a family of 4 siblings, each with different severities of MELAS, using safe, non-invasive tests. We will determine whether there is a decrease in the ability of small brain blood vessels to increase blood flow by dilating in response to certain strong stimuli such as increased blood carbon dioxide levels or in response to brain cell activation in the vision centre by strong visual stimuli. We will use a technique called BOLD-fMRI which can detect changes in brain blood flow. As exercising muscle also depends on increased blood flow and mitochondrial energy, we will study different measures of aerobic energy metabolism in exercising muscle using cycle exercise testing and special phosphorus-magnetic resonance spectroscopy which measures the changes in the major chemicals of muscle energy metabolism. The dietary amino acid L-arginine is known to dilate blood vessels increasing blood flow and to decrease toxic free radicals that are generated by dysfunctional mitochondria. We will determine the effect of a single dose and a 6 week trial of L-arginine, on brain blood vessel reactivity, brain cell activation and muscle aerobic function to see how useful this would be in the treatment of these patients and other mitochondrial disorders which present with strokes.

## **RATIONALE**

Nitric oxide (NO) is synthesized from the amino acid L-arginine by nitric oxide synthases (NOS).

**A.** Tonic release of NO is a significant regulator of cerebral blood flow and is responsible for vasodilation (1). In brain, the relative importance of neuronal nNOS in neurons or perivascular nerves vs endothelial eNOS in cerebral vessels in the control of cerebral blood flow is unknown (1). NO generated by eNOS diffuses from the endothelium to smooth muscle where it increases cGMP leading to smooth muscle relaxation. **B.** NO also protects against peroxide-mediated cytotoxicity from reactive oxygen species (ROS) (2). Because MELAS (Mitochondrial Encephalomyopathy, Lactic Acidosis, Sroke-like episodes) patients have decreased L-arginine levels (3,4), vasodilatation may be significantly decreased. **C.** Further, as MELAS individuals have defective respiratory chain activity, a high NADH/NAD ratio could inhibit NOS further decreasing NO production. **D.** In addition, defective respiratory chain function in enlarged mitochondria documented in cerebrovascular endothelial and smooth muscle cells in MELAS (5,6) with bioenergetic compromise could also lead to aberrant vascular tone/autoregulation, resulting in local ischemia (7). **E.** Also, most MELAS mutations result in deficient Complex I activity (8) which may be associated with increased ROS production (9). Studies of acute and chronic L-arginine therapy in MELAS have suggested significant alleviation and potential prevention of stroke-like episodes (SLEs) (3,10,11). Improved cerebral hypoperfusion by SPECT scanning & major clinical improvement was demonstrated in one patient at the third SLE 2 hrs after intravenous (iv) L-arginine and in another patient on chronic L-arginine (10). Flow mediated vasodilation of brachial artery diameter as measured by ultrasound also showed improvement in MELAS patients 2 hrs after iv L-arginine (10). Thus, L-arginine may reduce ischemic damage in acute focal brain ischemia by (a) increasing microcirculation (12), (b) decreasing ROS damage (c) modulating neurotransmitters (13). In muscle, it may also increase capillary perfusion improving exercise capacity (14). Understanding the mechanisms of action of L-arginine in MELAS will foster development of more targeted therapies for this and other mitochondrial defects.

## **SIGNIFICANCE**

The current study has the potential to significantly improve our understanding of the molecular and vascular pathophysiology of MELAS which is not well understood at present. Recent work suggests neuronal cytopathy, small vessel angiopathy or a combination of the two are responsible for SLEs (15). If we can identify the fundamental underlying defect(s) in cerebrovascular, neuronal and muscle oxidative function in MELAS, we can recommend more targeted therapies to improve health, quality of life, and survival in these individuals. We will also have identified a tool that may help predict the risk of SLEs. This study will allow us to

Pilot study to investigate the efficacy of L-arginine therapy on endothelium-dependent vasodilation & mitochondrial metabolism in MELAS syndrome.

quantify the effect of L-arginine in MELAS patients and to correlate the physiological responses of muscle as measured by  $^{31}\text{P}$  MRS and the cerebrovascular response as measured by BOLD-fMRI. This will also have applications to individuals with secondary mitochondrial failure.

## **STUDY AIMS**

1. To determine the efficacy and primary mechanism (s) of action of L-arginine in MELAS syndrome by quantifying the effect of L-arginine on (a) cerebrovascular reactivity (CVR) to  $\text{CO}_2$  stimulus (b) neuronal cell activation of CVR and (c) muscle oxidative function in MELAS siblings with the common 3243 A>G mutation.
2. To determine the relative contributions of impaired microvascular endothelial cell function vs impaired neuronal cell activation of CVR in MELAS syndrome.
3. (a) To determine the efficacy of BOLD-fMRI (tool to measure CVR) to differentiate between impaired CVR in a family with variable CNS severity of MELAS compared to controls (b) to determine whether a relationship exists between the severity of neurological phenotype and degree of impairment of CVR as a prognostic predictor for risk of stroke. (\* % mutant mtDNA blood may not correlate with % mutant mtDNA in brain, muscle or heart).

## **STUDY PLAN**

Brain BOLD-fMRI allows us to examine CVR non-invasively *in vivo* in 4 MELAS sibs vs 4 age-, sex- and menstrual cycle- matched normal controls. To determine the relative contributions of (a) impaired isolated microvascular endothelial cell function in response to changes in  $\text{PCO}_2$  (using a rebreathing circuit) vs (b) impaired occipital neuronal cell (in response to a strong visual stimulus) activation of CVR, we will study both paradigms using brain BOLD-fMRI. Given the variable severity of neurological phenotypes in this family, we will determine the relationship between the severity of the phenotype and the degree of dysfunction in CVR to  $\text{PCO}_2$  vs neuronal stimulus. This correlation may provide a useful tool for predicting the risks for SLEs. To determine the correlation between brain and muscle dysfunction, we will compare brain BOLD-fMRI findings with parameters of total body and muscle oxidative function as determined by maximal incremental cycle ergometry and  $^{31}\text{P}$ -MRS of exercising muscle, respectively. Following these baseline studies, we will then quantify the effect, in only our MELAS sibs, of L-arginine (single oral dose & 6 wk steady state trial) on CVR, neuronal activation, and total body and muscle oxidative function to determine which function(s) is improved. Absorption and exhaled NO production and urine NOx will be measured.

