### **PREDICTED OUTCOMES**

1. We predict the severity of reduction in CVR in MELAS patients will be directly proportional to the severity of the neurological phenotype. The BOLD signal in brain will be decreased because of decreased cerebrovascular reactivity due to (a) endothelial cell dysfunction and/or (b) decreased neuronal cell activation of blood flow.
2. There will be a direct correlation between the degree of oxidative dysfunction in muscle, decrease in total body maximal aerobic capacity and impairment of CVR in MELAS which will be directly proportional to the severity of the neurological phenotype.
3. L-arginine will improve CVR to (a) CO2 stimulus and (b) neuronal cell activation, as well as total body maximal aerobic capacity and muscle oxidative function by increasing microvascular (arteriolar) endothelium-dependent vasodilation and thus flow. L-arginine will also improve neuronal cell mitochondrial function.

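### The CO2 response (endpoint C1) is labelled a test of isolated endothelial function, but on the protocol's own rationale it cannot separate endothelial from smooth-muscle failure

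*Protocol*

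**What the plan says.** The Study Plan pairs two brain BOLD-fMRI paradigms. The CO2 rebreathing paradigm is said to address "impaired isolated microvascular endothelial cell function in response to changes in" PCO2. The visual paradigm is said to address occipital neuronal activation of cerebrovascular reactivity (CVR). Aim 2 is built on that pairing: "To determine the relative contributions of impaired microvascular endothelial cell function vs impaired neuronal cell activation of CVR in MELAS syndrome".

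Predicted Outcome 1 offers two causes of a reduced BOLD signal, endothelial dysfunction and reduced neuronal activation of flow, alone or together. Predicted Outcome 3 attributes the expected benefit of L-arginine to endothelium-dependent vasodilation, a term that is also in the study title. It adds that "L-arginine will also improve neuronal cell mitochondrial function".

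The Rationale is broader. Item D describes defective respiratory chain function in enlarged mitochondria "documented in cerebrovascular endothelial and smooth muscle cells in MELAS" and says that this could disturb vascular tone and autoregulation. Item A says that NO made in the endothelium "diffuses from the endothelium to smooth muscle where it increases cGMP leading to smooth muscle relaxation". It also leaves open how much the neuronal and the endothelial NO synthase each contribute to regulating blood flow in the brain.

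Other parts of the protocol use neutral terms. Aim 1 and the Analysis section refer simply to CVR to a CO2 stimulus, and item 3 of How Data Will Be Utilized contrasts microvascular reactivity with neuronal activation.

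**The concern.** The word *isolated* claims that the CO2 response reflects one cell type. If the vessel wall has a second affected cell type, and the response has to pass through it, the endpoint measures the two together.

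Aim 2 is at stake, because it asks for the relative contribution of the endothelium. So is the mechanistic part of Predicted Outcomes 1 and 3. The protocol intends its mechanistic findings to guide more targeted therapies and its pilot data to shape a larger trial. An attribution that the measurement cannot support would carry over into both. It is a question of what the endpoint can identify, separate from the low power that the Analysis section openly admits.

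**Working it through.** No arithmetic applies. The protocol gives no figure on this point, so the check sets its statements side by side.

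**1. What C1 is said to measure.** Study Plan: isolated microvascular endothelial function. Aim 2: the endothelial side of "impaired microvascular endothelial cell function vs impaired neuronal cell activation of CVR in MELAS syndrome". Predicted Outcome 1: endothelial dysfunction is the only vascular cause named.

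**2. What the Rationale says a vascular response depends on.** Item A gives a chain: endothelial NO synthase makes NO, NO reaches smooth muscle, and smooth muscle relaxes. The observed flow change comes at the end of that chain.

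**3. Where the Rationale puts the defect.** Item D puts it in endothelium and in smooth muscle, so both links may be impaired. The documents give no weights for the two.

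**4. What follows for a low C1.** Two patterns give the same observation:

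| | Endothelial signal | Smooth-muscle relaxation | C1 |
|---|---|---|---|
| Pattern 1 | impaired | intact | low |
| Pattern 2 | intact | impaired | low |

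There is one measured quantity and at least two possible sources. A larger sample would estimate C1 more precisely without dividing it between them.

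**5. Whether another scheduled test separates the patterns.** The key to Table 1 lists two BOLD stimuli, CO2 and visual, and the Analysis section names C1 and C2. No endothelium-independent vasodilator comparator is listed. The visual response adds a neuronal step, but it is still read out as a vascular response, so setting C2 beside C1 does not divide the vascular part into endothelium and muscle.

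**6. Whether the L-arginine response separates them.** The Rationale describes L-arginine as the substrate of NO synthases in general and leaves the shares of the neuronal and endothelial forms open. It also lists reduced oxidative damage and modulation of neurotransmitters among possible actions. A rise in C1 on L-arginine is therefore compatible with an endothelial mechanism but does not establish it.

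**7. Whether the NO measurements help.** The section on exhaled NO presents it as a lower-airway measure and the urine metabolites as a reflection of systemic NO production. Neither locates NO in cerebral vessels.

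**8. The neuronal mitochondrial prediction.** The Analysis endpoints are quadriceps 31P-MRS, maximal oxygen uptake with work capacity, and the two CVR measures. None measures neuronal mitochondria directly. C2 is a blood-flow response to neuronal activation.

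**The case against.** The strongest reply is that the endothelial label is confined to a few phrases. Aim 1 and the Analysis section name the endpoint neutrally, item 3 of How Data Will Be Utilized already uses the broader contrast, and the Study Plan itself reverts to CVR to PCO2 shortly afterwards. Predicted Outcomes are hypotheses, and no rule says that a low C1 must be reported as endothelial dysfunction. This is a pilot in 4 siblings whose stated analytic output is means and SDs for a later study. All of that is right, and it limits the scope. It does not rescue aim 2 or the word *isolated*, which the Rationale contradicts.

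A second reply is that the BOLD method text is not visible: section C of the Analysis shows its heading and then moves to NO measurement. A control condition or a justification for the CO2 paradigm could stand there. That cannot be excluded, although the Table 1 key makes a third stimulus unlikely.

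Some stronger readings are tempting and should be resisted:

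- A reader might infer that the Rationale also places the defect in neuronal NO synthase. It does not. Item A states only that the relative importance of the two forms is unknown, and item C says that NO synthase, form unnamed, could be inhibited.
- A reader might say that smooth muscle is equally likely to be the source, or that the endothelial share lies anywhere from 0 to 100%. The documents give no weights. That range only restates that the share is not identified.
- A reader might hold that aim 1 and item 3 of How Data Will Be Utilized fall with the label. Neither uses it.

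**Conclusion.** The point holds in limited form. The Study Plan's description of C1 as isolated endothelial function conflicts with the Rationale, and aim 2 and Predicted Outcomes 1 and 3 rest on that description. On the visible text C1 measures microvascular reactivity to CO2, with endothelium and smooth muscle combined.

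The effect is on interpretation. It narrows what aim 2 can conclude and leaves every endpoint, comparison, visit and sample size as it is. The contrast between a CO2-evoked and a neuronally evoked response remains usable. No numerical size can be given, because the documents contain no figure from which to derive the endothelial share.

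The conclusion assumes that Table 1 lists all BOLD stimuli and that the unseen BOLD methods contain no endothelium-independent comparator. If they do contain one, the protocol should point to it in aim 2.

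**What to change.** All changes are to wording:

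- **Study Plan:** delete *isolated* and describe the CO2 paradigm as testing microvascular reactivity to CO2.
- **Aim 2:** contrast impaired microvascular reactivity with impaired neuronal activation, in line with item 3 of How Data Will Be Utilized.
- **Predicted Outcome 1:** make cause (a) vascular dysfunction, endothelial and/or smooth muscle.
- **Predicted Outcome 3:** present endothelium-dependent vasodilation as a hypothesis that C1 alone cannot confirm. Mark the prediction on neuronal mitochondrial function as not directly tested by the listed endpoints.
- **Analysis:** add one sentence saying that a low C1 is compatible with endothelial or smooth-muscle dysfunction.

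It would be a mistake to replace the label with a rule that calls any part of C1 moving with exhaled NO or urine metabolites NO-dependent. Those measures do not capture cerebral NO, so the attribution would again be unsupported.

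No new test, visit or participant is needed. The cost is a narrower mechanistic claim.

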### **PREDICTED OUTCOMES**

1. We predict the severity of reduction in CVR in MELAS patients will be directly proportional to the severity of the neurological phenotype. The BOLD signal in brain will be decreased because of decreased cerebrovascular reactivity due to (a) endothelial cell dysfunction and/or (b) decreased neuronal cell activation of blood flow.
2. There will be a direct correlation between the degree of oxidative dysfunction in muscle, decrease in total body maximal aerobic capacity and impairment of CVR in MELAS which will be directly proportional to the severity of the neurological phenotype.
3. L-arginine will improve CVR to (a) CO2 stimulus and (b) neuronal cell activation, as well as total body maximal aerobic capacity and muscle oxidative function by increasing microvascular (arteriolar) endothelium-dependent vasodilation and thus flow. L-arginine will also improve neuronal cell mitochondrial function.

### **HOW DATA WILL BE UTILIZED:**

1. To develop parameters for an expanded clinical trial with a larger cohort of MELAS patients based upon the predicted numbers needed to establish statistical significance for the observed outcome measures. This would be based upon the trends observed in our pilot study.
2. To determine the utility and sensitivity of BOLD-fMRI (as a tool to measure CVR) to differentiate between the different severities of neurological phenotypes in a small cohort of heteroplasmic siblings and to identify trends or a threshold for the prognostic prediction for risk of stroke. This could be important also in a given individual as the % mutant mtDNA increases with aging and exogenous mitochondrial stressors (e.g. XRT, toxins, viruses).
3. To increase understanding about the relative contributions of impaired microvascular reactivity versus impaired neuronal cell activation in the pathogenesis of SLEs in MELAS syndrome to develop more targeted therapies.

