### **ANALYSIS:**

The following comparisons will be made **(1)** MELAS sibs will be compared to themselves both on L-arginine (single oral dose and 6 wk steady state trial) vs. off L-arginine (pre-trial baseline) to evaluate effects of treatment. **(2)** They will be seen post L-arginine therapy to determine if there are lasting effects up to 8 wks vs. off L-arginine (baseline). **(3)** MELAS sibs at baseline vs. controls **(4)** MELAS sibs on L-arginine (single oral dose and 6 wk steady state trial) vs. controls. Four different end-points will be compared **(A)**  $^{31}\text{P}$ -MRS study of quadriceps for PCr recovery and ATP levels **(B)** maximal oxygen uptake  $\text{VO}_{2\text{max}}$  (ml  $\text{O}_2$ /kg/min) and mean peak work capacity (Watts/kg) **(C1)** CVR to  $\text{CO}_2$  stimulus **(C2)** CVR to neuronal stimulus. Comparisons will be made of the different parameters and to determine whether there are clinically significant differences between the MELAS sib groups (treated vs untreated), and MELAS sib vs control groups (Student's t-test). We understand that the sample size has insufficient power to detect statistically significant differences. However estimates of means and SD's obtained from this pilot study will be used in a future study to determine adequate sample sizes to detect statistically significant differences in these parameters.

**A. P-Magnetic resonance spectroscopy protocol – Muscle function investigation:** We will study exercising quadriceps using our MR-compatible up-down ergometer and our well established aerobic exercise protocol at 65 % of maximal voluntary contraction (25). Testing will be done between 60 to 105 minutes after an oral L-arg dose of 200 mg/kg to ensure maximum serum arg at time of exercise. **Predicted outcome:** Untreated sibs: P-MRS of quadriceps will show a delay in PCr recovery/resynthesis after exercise, reflecting the reduced ATP synthesis rate compared to controls. We predict that the degree of delay in PCr recovery will be directly proportional to the % mutant mtDNA in blood. Following L-arginine, we predict a faster PCr recovery/resynthesis after exercise and increased ATP levels. P-MRS data will be collected on our GE Twin Speed EXCITE™ III 12.0 1.5 Tesla imaging & spectroscopy system at HSC

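### Aim 3(b) treats CVR impairment as a predictor of stroke risk, but a cross-section of four siblings with no stroke-like-episode endpoint cannot estimate prognosis or a threshold; separately, the blood-mtDNA prediction for PCr recovery conflicts with the protocol's own caveat

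*Protocol*

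**What the plan says.** **The predictive claim** appears in four places in the protocol.

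- Study Aims, Aim 3(b), asks whether severity of the neurological phenotype is related to "degree of impairment of CVR as a prognostic predictor for risk of stroke".
- How Data Will Be Utilized, item 2, plans "to identify trends or a threshold for the prognostic prediction for risk of stroke".
- Significance states "We will also have identified a tool that may help predict the risk of SLEs".
- Study Plan says the severity-CVR correlation may turn out useful for predicting stroke-like episodes (SLEs).

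**The data behind it** are "4 MELAS sibs vs 4 age-, sex- and menstrual cycle- matched normal controls", with the controls tested once at baseline. The Analysis section says "Four different end-points will be compared" and lists <sup>31</sup>P-MRS, maximal oxygen uptake with peak work, CVR to CO<sub>2</sub> and CVR to a neuronal stimulus. Table 1 runs from week 0 to week 20.

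**The severity yardstick** differs by section. Predicted Outcomes, items 1 and 2, expects CVR impairment, muscle oxidative dysfunction and loss of aerobic capacity to be "directly proportional to the severity of the neurological phenotype". Analysis, part A, predicts instead that "the degree of delay in PCr recovery will be directly proportional to the % mutant mtDNA in blood". The note to Aim 3 warns that the percentage of "mutant mtDNA blood may not correlate with % mutant mtDNA in brain, muscle or heart".

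**The concern.** A prognostic predictor links a measurement taken now to an event that happens later. A threshold needs people with and without that event on either side of a cut-off. This design supplies the measurement but not the event. What it can show is whether siblings who are more severely affected today also have lower CVR today. That pattern would appear equally if low CVR precedes SLEs or if damage from past SLEs lowers CVR.

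At stake is what the trial may conclude. If the aims stay as written, a matching order in four relatives could be read as support for a stroke-risk tool.

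The second issue is smaller and concerns muscle only. Two severity orderings are offered for PCr recovery with no stated precedence, and one of them uses a marker that the protocol itself doubts. If the two orderings differ among the siblings, it is unclear which one the muscle result is meant to test.

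**Working it through.** The protocol gives no sample-size, correlation or threshold calculation, so there is no figure to reproduce. The check has three parts.

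**1. Is there an outcome to predict?**

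- Endpoints (Analysis): the four groups listed above. None is an SLE or stroke.
- Schedule (Table 1): no visit records SLEs as an outcome, although an episode could surface as an adverse event.
- Observation time: 4 siblings × 20 weeks / 52 = 1.5 person-years, part of it on L-arginine.
- Expected events, if SLEs were counted: the protocol gives no rate. At assumed rates of 0.1 to 1 per person-year, 1.54 × 0.1 = 0.15 up to 1.54 × 1 = 1.5 events in total.

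**2. What can n = 4 show about an ordering?** Alpha = 0.05 is an assumption.

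- *Rank agreement.* There are 4! = 24 orderings. Perfect agreement in the predicted direction has probability 1/24 = 0.042 (one-sided); in either direction 2/24 = 0.083 (two-sided).
- *Pearson correlation.* The critical value is r = t/√(t² + 2), with 2 degrees of freedom. Two-sided, t = 4.303: 4.303/√(18.52 + 2) = 0.950. One-sided, t = 2.920: 2.920/√(8.53 + 2) = 0.900.
- *Precision.* The Fisher-z standard error is 1/√(4 − 3) = 1. For an observed r of 0.80, z = 1.099 and the 95% limits are tanh(1.099 ± 1.96) = −0.70 to 0.996.
- *Threshold.* Suppose the siblings could be split into affected and unaffected. A cut-off in the predicted direction separates them perfectly by chance with probability 1/C(4,2) = 1/6 for a 2 vs 2 split, or 1/C(4,1) = 1/4 for 1 vs 3. The exact 95% lower limit for a sensitivity of k out of k is 0.025^(1/k): 16% for 2 of 2 and 29% for 3 of 3.

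**3. Severity scale, section by section.**

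| Measure | Scale named | Where |
|---|---|---|
| CVR (both stimuli) | neurological phenotype | Study Aims, Study Plan, Predicted Outcomes |
| Muscle oxidative function, aerobic capacity | neurological phenotype | Predicted Outcomes, item 2 |
| PCr recovery | mutant mtDNA in blood | Analysis, part A |
| Maximal oxygen uptake, peak work | mutant mtDNA, tissue not named | Analysis, part B |

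PCr recovery can be proportional to both phenotype and blood load only if those two track each other across the siblings. The note to Aim 3 says that blood load need not track load in brain or muscle.

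**The case against.** The strongest defence is that this is an openly labelled pilot. Significance, Study Plan and the data-use section all hedge. Trends are to feed a larger cohort, and the Analysis section concedes that the sample is too small to show significant differences and reserves the means and SDs for sizing a later study. Much of this stands: a reader should not infer that the protocol promises a validated threshold. The word threshold is not in Aim 3 at all; it occurs only in the data-use section, as an alternative to trends. But the power concession concerns group differences by t-test. It does not withdraw the predictor, and a larger alpha or a hedge does not supply a missing outcome.

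Other stronger readings are tempting and should be resisted.

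- *That the sponsor may choose the severity scale that suits the stroke claim.* For CVR, every section names neurological phenotype. The second scale affects muscle and aerobic measures only, and these carry no stroke-risk claim.
- *That a chance match is likely.* For the two CVR measures, perfect agreement in at least one has probability 1 − (23/24)² = 8% if they are independent, and less if they are positively correlated.
- *That no ordering could reach 0.05.* This is true two-sided only. The predictions are directional, and one-sided p is 0.042. Nor does the protocol specify a correlation test, so these figures show how little n = 4 can say rather than criticise a planned test.
- *That all the mtDNA predictions contradict the caveat.* Only the PCr prediction names blood, and the caveat says blood load may fail to correlate, not that it does.

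The public text is also incomplete where subjects are described, and it may have held SLE history or mtDNA loads. Past history in four relatives would still support only a retrospective association. A SAP could define a severity grading, but it could not create an outcome that the study does not follow.

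**Conclusion.** The point holds in two separate parts.

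**Prediction.** Aim 3(b) and the matching statements ask for a property the design does not have. With no SLE endpoint, neither prognosis nor a threshold is estimable, and the direction between low CVR and past episodes cannot be settled. This conclusion rests on the listed endpoints and the timetable and needs no assumed alpha. The n = 4 figures (p no lower than 0.083 two-sided or 0.042 one-sided for ranks; critical |r| of 0.95; interval −0.70 to 0.996 around r = 0.80) show that even the cross-sectional relation would be very imprecise. They do assume a 5% level or 95% intervals.

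**Muscle scale.** The blood-mtDNA prediction for PCr recovery is at odds with the note to Aim 3 and with Predicted Outcomes, item 2. This is an inconsistency to reconcile. It is not evidence of selective analysis and has no bearing on the stroke-risk claim.

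Neither part affects the measurements, the treatment comparison or the pilot's use for sizing a later study. The change should be made because it governs what the trial may conclude.

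**What to change.** 1. Restate Aim 3(b), and the matching text in Significance, Study Plan and How Data Will Be Utilized, item 2, as a descriptive, hypothesis-generating cross-sectional ordering of CVR by neurological severity, with each sibling's values shown individually.
2. Remove the prognostic and threshold claims. State that prediction is left to a larger cohort with stroke-like episodes as an outcome.
3. Reconcile Analysis, part A, with the note to Aim 3 and Predicted Outcomes, item 2: name one severity ordering for the muscle endpoints before results are seen, and treat the other as descriptive. Either choice is workable; what matters is that it is fixed in advance. The same edit can name the tissue meant in part B.

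The cost is wording only, with no change to visits, tests or participants. The sponsor gives up a claim that these data cannot support.
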